## Abstract

**Background:**

Bacteremia is a leading cause of mortality and morbidity in critically ill adults. No previous randomized controlled trials have directly compared shorter versus longer durations of antimicrobial treatment in these patients.

**Methods/Design:**

This is a multicenter pilot randomized controlled trial in critically ill patients with bacteremia. Eligible patients will be adults with a positive blood culture with pathogenic bacteria identified while in the intensive care unit. Eligible, consented patients will be randomized to either 7 days or 14 days of adequate antimicrobial treatment for the causative pathogen(s) detected on blood cultures. The diversity of pathogens and treatment regimens precludes blinding of patient and clinicians, but allocation concealment will be extended to day 7 and outcome adjudicators will be blinded. The primary outcome for the main trial will be 90-day mortality. The primary outcome for the pilot trial is feasibility defined by (i) rate of recruitment exceeding 1 patient per site per month and (ii) adherence to treatment duration protocol ≥ 90%. Secondary outcomes include intensive care unit, hospital and 90-day mortality rates, relapse rates of bacteremia, antibiotic-related side effects and adverse events, rates of *Clostridium difficile* infection, rates of secondary infection or colonization with antimicrobial resistant organisms, ICU and hospital lengths of stay, mechanical ventilation and vasopressor duration in intensive care unit, and procalcitonin levels on the day of randomization, and day 7, 10 and 14 after the index blood culture.

**Discussion:**

The BALANCE pilot trial will inform the design and execution of the subsequent BALANCE main trial, which will evaluate shorter versus longer duration treatment for bacteremia in critically ill patients, and thereby provide an evidence basis for treatment duration decisions for these infections.

**Trial registration:**

The Pilot Trial was registered on 26 September 2014. Trial registration number: NCT02261506.

**Electronic supplementary material:**

The online version of this article (doi:10.1186/s13063-015-0688-z) contains supplementary material, which is available to authorized users.

## Background

Bacteremia is a common and serious problem affecting 15% of critically ill patients and resulting in a threefold higher mortality [1,2]. Among survivors, bacteremia is associated with a 2 to 7 day prolongation of intensive care unit (ICU) length of stay, a 2 to 3 week prolongation of hospital stay, and $25,000 to $40,000 in attributable excess costs [3,4].

The ICU is the location of greatest antimicrobial use in most hospitals; however, audits have revealed that 30 to 50% of antibiotic use in the ICU is unnecessary or inappropriate [5-7] and leads to avoidable drug side effects. Antibiotics are among the most common cause of serious adverse drug events [8], which occur in up to 5 to 10% of inpatient recipients [9]. Excessive durations of antibiotic therapy are the greatest contributor to inappropriate antibiotic use in acute care hospitals, long-term care facilities, and ambulatory care [6,10-12]. Discontinuing antibiotics after achieving clinical cure can potentially reduce the burden of adverse events (allergy and organ toxicity), *Clostridium difficile* infections, and additional costs and morbidity related to selection of antimicrobial resistant pathogens [13,14] Antibiotic resistance rates are rising among pathogens in ICUs [15] at the same time as the drug discovery pipeline is diminishing with very few new antimicrobial agents under development [16,17].

Meta-analysis of randomized controlled trials has demonstrated that shorter duration antibiotic therapy is as effective as longer duration antibiotic therapy for a range of mild to moderate infections [18]. Even in critically ill patients with ventilator-associated pneumonia, mortality rates and relapse rates were non-inferior among the 402 patients (of which only 7% were bacteremic) randomized to receive shorter (8 day) versus longer (15 day) courses of antibiotics [19]. However, similar high-grade evidence is lacking for the treatment of patients with bloodstream infections [1,20,21]. Specific guidelines for treatment durations exist for a variety of infections in ICU, including pneumonia [22,23], intra-abdominal infection [24], catheter-related bloodstream infection [25], pyelonephritis [26], and skin and soft tissue infection [27] but no guidelines exist for the optimal duration of treatment for bacteremic patients.

We have performed a systematic review of the existing literature [21], a national practice survey of Infectious Diseases (ID) and critical care physicians [28], a single center observational study [29], and a multicenter observational study [[name], [name], [name], [name], [name], [name], et al: Antibiotic Treatment Durations Among Canadian Critically Ill Patients with Bacteremia, forthcoming]. We have identified gaps in current evidence, documented extensive practice variation, and confirmed equipoise for a randomized controlled trial comparing shorter (7 days) versus longer (14 days) antibiotic treatment durations for bloodstream infections.

The primary aim of the Bacteremia Antibiotic Length Actually Needed for Clinical Effectiveness (BALANCE) main randomized controlled trial will be to determine whether 7 days (as compared to 14 days) of adequate antibiotic treatment is associated with non-inferior survival for critically ill patients with bacteremia. The aim of this BALANCE pilot randomized controlled trial is to determine whether recruitment and protocol adherence rates will be sufficient for the main trial to be feasible.

## Methods/Design

### Design

We will conduct a multicenter randomized concealed allocation trial of shorter duration (7 days) versus longer duration (14 days) antibiotic treatment for critically ill patients with bacteremia admitted to ICU.

### Setting

To maximize efficiency, the BALANCE pilot trial will aim to involve a geographically and clinically diverse spectrum of ICUs across Canada. The study will be initiated in October 2014 at Sunnybrook Health Sciences Centre (SHSC) in Toronto, Ontario, and then rolled out to additional sites, starting with Kingston General Hospital in Kingston, Ontario. These two sites will be sufficient to accrue the intended pilot sample size of 115 patients, but we aim to roll out to 13 additional sites, if sufficient funding is acquired, to improve external generalizability of the pilot trial findings. See Additional file 1 for participating pilot sites.

### Population

All patients aged ≥18 years will be considered for enrolment in this study if they meet all the inclusion and no exclusion criteria.

#### Inclusion criteria

Patient is in the ICU at the time a blood culture result is reported as positive with a pathogenic bacterium.

#### Exclusion criteria

Patient has severe immune system compromise, as defined by: absolute neutrophil count <0.5×10^9^/L; or is receiving immunosuppressive treatment for solid organ or bone marrow or stem cell transplant.Patient has a prosthetic valve or synthetic endovascular graft.Patient has a suspected or documented syndrome with well-defined requirement for prolonged treatment (infective endocarditis, osteomylitis/septic arthritis, undrainable/undrained abscess, or unremovable/unremoved prosthetic-associated infection).Patient has a single positive blood culture with a common contaminant organism according to the Clinical Laboratory & Standards Institute (CLSI) (coagulase negative staphylococci, *Bacillus spp., Corynebacterium spp., Propionobacterium spp., Aerococcus spp., Micrococcus spp*) [30].Patient has a positive blood culture with *Staphylococcus aureus* [31].Patient has a positive blood culture with *Candida spp.* or other fungal species as the only potential pathogen.Patient already or previously enrolled in the trial.

### Eligible, nonrandomized patients

We will maintain a log of all patients who were eligible but not randomized due to one of the following reasons:Patient or substitute decision maker (SDM) declined consent, specifying reason;Patient unable to give consent and SDM not available;ICU physician declined consent, specifying reason; [32]Consent not obtained due to other reason, specifying reason.

### Ethics and informed consent

The study protocol has been approved by the Sunnybrook Health Sciences Research Ethics Board and the Queen’s University Health Sciences and Affiliated Teaching Hospitals Research Ethics Board (for Kingston General Hospital), and will be sought at other participating sites. After seeking permission from the treating team, the research coordinator/site primary investigator will approach eligible patients (or their substitute decision-makers) as soon as their blood cultures are positive to obtain informed consent (see Additional file 2). Consent can be delayed at maximum to the 7th day of adequate antibiotic treatment. Critically ill patients are frequently unable to provide initial consent due to altered level of consciousness or understanding. Hence, the Canadian Critical Care Trials Group (CCCTG) has standard operating procedures to seek assistance from substitute-decision makers on behalf of patients. This process has been found feasible and acceptable to patients, decision-makers, and research ethics boards across Canada and has been successfully employed among dozens of CCCTG RCTs [32-35]. We will use this enhanced approach to consent, employing 13 previously described strategies distributed over three phases: preparation for the consent encounter, the consent encounter, and as follow-up to the consent encounter [34].

### Randomization and allocation concealment

Randomization will occur as soon as the consent is obtained. The web-based randomization system for BALANCE will be created using RANDOMIZE.NET (http://www.randomize.net/), and will employ variable block sizes, stratified by ICU site. After the full susceptibility results become available, the site research coordinator along with site co-investigators will determine the date for day 7 unblinding, taking into account the number of days that the patient has already received adequate antibiotics after the blood culture collection date. At day 7 (date entered by the research coordinator), another email will be sent with the unblinded treatment assignment for the patient. At this time the unblinded treatment for that patient will be displayed in the reports available to the site research coordinator. If a patient is randomized to the shorter (7 day) treatment arm, the treating team will be informed to stop the antibiotics at the completion of 7 days of antibiotics appropriate for the causative pathogen; if the patient is randomized to the longer (14 day) arm the team will be instructed to continue the antibiotic until that date.

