### Statistical analysis

#### Sample size

To estimate our expected adherence rate of 90% within a margin of error of ± 5% (that is, actual adherence 85 to 95%), with 95% confidence, we plan to enroll 115 patients. At our expected recruitment rate of 1 patient/site month across 15 sites, we will need approximately 10 to 24 months to recruit these 115 patients given variability in site trial start-up steps (REB approval, data sharing agreements and contracts). By the time we have recruited 115 patients, we will know with 95% confidence that this number of sites would be able to recruit 95 to 138 patients over the same time interval in a future trial; this data will then be used to estimate the number of centers needed for the main trial (see Additional file 1 for detailed sample size calculation).

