### Analysis of secondary outcomes

Mortality rates (at ICU discharge, hospital discharge and 90 days) will be measured as the proportion of patients alive or dead at these time points. We hypothesize that mortality rates will be non-inferior with 7 days of treatment; the main BALANCE trial will be powered to test this hypothesis. Continuous secondary outcomes, including lengths of stay in ICU and hospital, and durations of ventilation and vasopressor use, will be compared by Wilcoxon test. We will compare the ‘difference in differences’ between day 7 to 14 procalcitonin levels in the two treatment groups.

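### Allocation is blocked within ICU site, but the Wilcoxon comparisons name no site term; read as unstratified they are mildly conservative and forgo part of the precision from stratifying

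*Protocol article*

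**What the plan says.** Two sections of the protocol article matter here.

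- **Randomization and allocation concealment:** the web-based system "will employ variable block sizes, stratified by ICU site". Block sizes are not given.
- **Analysis of secondary outcomes:** lengths of stay in ICU and hospital, and "durations of ventilation and vasopressor use, will be compared by Wilcoxon test". No strata, site term or adjustment is named, and none is excluded.

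The scale comes from the Sample size and Setting sections. The target is stated as "with 95% confidence, we plan to enroll 115 patients". The number of ICUs could lie anywhere between the planned fifteen ("At our expected recruitment rate of 1 patient/site month across 15 sites") and the minimum of two ("These two sites will be sufficient to accrue the intended pilot sample size of 115 patients"). No significance level, power, effect size or between-site variance is stated for these secondary comparisons.

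**The concern.** Blocking within site nearly equalises the arms inside each ICU, so a site with long stays contributes about equally to both arms and cannot distort the treatment contrast. The usual rank-sum variance takes no account of this. It assumes that any split of the 115 patients was possible, so it includes variation between sites that the design has already removed. The standard error is then too large and the test rejects too rarely.

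The Setting section aims for a geographically and clinically diverse set of ICUs, so some difference between sites in stay and ventilation is plausible. How large it would be is not stated. At stake is power in the secondary comparisons, and the risk that the same convention carries into the main trial. The Trial status section foresees pilot patients being rolled into it if no substantive protocol change is needed.

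**Working it through.** **Figure to reproduce.** The article states no error rate or power for these comparisons, so there is none to reproduce. The 115 was set for precision on adherence and is used here only as an input.

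**Inputs from the article.** N = 115; 2 or 15 sites; blocks within site; Wilcoxon test.

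**Assumptions.** Two-sided 5% level; equal site sizes; block sizes 2/4 (4/6 also tried); a shift of 0.53 SD, chosen to give about 79% power; ICC from 0 to 0.30. Working on a normal scale costs nothing for the ordinary test, because ranks do not change under a log transformation of stay.

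**Approximation.** With near-perfect balance within sites, the true standard error is √(1 − ICC) times the one the unstratified test uses. Hence:

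- type I error ≈ 2Φ(−1.96/√(1 − ICC))
- λ = 0.53 × √(115/4) × √(3/π) / √(1 − ICC) = 2.777/√(1 − ICC)
- power, unstratified ≈ Φ(λ − 1.96/√(1 − ICC)); power, site-aligned ≈ Φ(λ − 1.96)

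| ICC | Type I error | Power, unstratified | Power, site-aligned |
|---|---|---|---|
| 0.05 | 2Φ(−2.011) = 4.4% | Φ(0.838) = 79.9% | Φ(0.889) = 81.3% |
| 0.20 | 2Φ(−2.191) = 2.8% | Φ(0.914) = 82.0% | Φ(1.145) = 87.4% |
| 0.30 | 2Φ(−2.343) = 1.9% | Φ(0.976) = 83.6% | Φ(1.359) = 91.3% |

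**Simulation** (10,000 runs per cell, blocks 2/4; unstratified v site-aligned, %):

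| ICC | 15 sites: type I | 15 sites: power | 2 sites: type I | 2 sites: power |
|---|---|---|---|---|
| 0.02 | 4.6 v 4.8 | 78.0 v 78.1 | 4.3 v 4.6 | 79.1 v 79.7 |
| 0.05 | 4.6 v 5.0 | 79.1 v 80.7 | 4.4 v 4.8 | 79.1 v 80.8 |
| 0.10 | 4.2 v 4.9 | 79.3 v 82.0 | 3.7 v 4.7 | 80.1 v 83.0 |
| 0.20 | 2.9 v 4.7 | 81.2 v 86.4 | 2.8 v 4.9 | 80.5 v 86.9 |
| 0.30 | 2.3 v 4.9 | 82.0 v 90.1 | 1.8 v 4.7 | 81.3 v 91.0 |

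Across both block-size choices, type I error of the unstratified test was 2.8 to 3.5% at ICC 0.20 and 1.6 to 2.6% at 0.30. As a control, unblocked randomization with 15 sites at ICC 0.20 gave 5.0%, so the deficit comes from the blocking.

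**Sensitivity to the set-up.** With a shift of 0.55 SD, 15 sites give 84% v 89% at ICC 0.20 and 85% v about 91% at 0.30. The two-site result depends on how the site difference is generated. The table fixes the sites one between-site SD either side of the mean, and the gap at ICC 0.30 is 91.0 − 81.3 = 9.7 points. If the two site effects are drawn at random, with a 0.55 SD shift, the gap is about 3 points at ICC 0.20 and 4 at 0.30 (88% v 92%). Roughly 3 to 8 points covers the 15-site runs and the two-site runs with random effects; the fixed two-site contrast is the extreme.

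**Which site-aware test.** With 15 sites of about 8 patients, van Elteren has less power than the plain test at low ICC: 74.8% v 78.4% at 0.05 and 77.1% v 79.1% at 0.10. With two sites it does well: 87.0% v 81.1% at ICC 0.20.

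**The case against.** The strongest objection is that a site-blind analysis is inferred from silence. The article names a test family, and a condensed article commonly leaves stratification of a secondary test to an analysis plan, which is not shown here. This stands as a limit: the point is conditional on reading the Wilcoxon test in its ordinary two-group sense. It does not remove the point, because the article does choose a test, and its literal application would leave out the factor used in randomization.

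A reader might infer stronger things that the article does not support:

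- **That power is lost wherever stays differ between sites.** At ICC 0.05 or less the loss is 0 to 2 points. It becomes material only near 0.2 or above, a value the article neither supports nor rules out.
- **That the gain from stratifying is thrown away.** The plain test keeps part of it: with 15 sites its power rises from 78.0% at ICC 0.02 to 82.0% at 0.30.
- **That false positives may result.** The error runs in the conservative direction.
- **That any stratified test is better.** Van Elteren can do worse with many small sites.

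A further objection concerns vasopressor duration, where some patients may have zero days: subtracting site averages from raw values would separate tied zeros. Ranking all patients first and then centring the ranks within site avoids this. In simulation with tied zeros that version held its level and lost at most about 1 point when sites did not differ.

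**Conclusion.** The point holds as a minor, low-cost improvement. If the Wilcoxon comparisons are run without regard to site after site-blocked allocation, they are conservative to a degree set by how far outcomes differ between ICUs. The effect is negligible at an assumed ICC of 0.05 or less. At 0.2 to 0.3, type I error is about 3% and roughly 3 to 8 points of power are forgone.

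These sizes rest on the assumed ICC, a shift of about half an SD, equal site sizes and small blocks, none of which the article supplies. The affected outcomes are secondary, in a pilot not sized for them. The recruitment and adherence criteria, reported with confidence intervals, do not depend on this choice.

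**What to change.** In Analysis of secondary outcomes, state that lengths of stay and durations of ventilation and vasopressor use will be compared between arms with a rank test that accounts for ICU site, the randomization stratum. Specify site-aligned ranks, with variance computed within site. Where many values tie at zero, rank all patients together and centre the ranks within site. Reserve van Elteren for the case where only a few large sites open.

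The cost is one clause: site is already recorded as the stratification factor, and no extra data are needed. The statistical downside is at most about 1 point of power if sites do not differ. If an unseen analysis plan already specifies how site enters these comparisons, a cross-reference is enough. It is best settled before outcomes are compared by arm, since pilot patients may be carried into the main trial.

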### Trial interventions

We will randomize patients to receive a shorter duration of adequate antimicrobial therapy (7 days) versus a longer duration (14 days). Adequate antimicrobial treatment will be defined as a regimen with *in vitro* activity against the organism(s) responsible for the bloodstream infection; the duration of adequate treatment will be determined as the cumulative number of calendar days for which adequate treatment is delivered beyond the date of collection of the index blood culture specimen- the clock will start from initiation of the first adequate treatment dose after the blood culture has been drawn. The selection of specific antimicrobial agents, doses and route of delivery will initially be at the discretion of the treating clinical team. Most commonly the patient will already be receiving some empiric antibiotic treatment for suspected infection prior to the blood culture being documented as positive; the study protocol will not expose patients to potential antibiotic treatment delays. As soon as blood culture results are available (preliminary Gram staining), the research coordinator, in consultation with the site investigator and site infectious diseases co-investigator if necessary, will review the initial antibiotic choice to ensure adequate empiric coverage for the potential culprit organism(s). As blood culture results are finalized (speciation and sensitivity determination), they will re-review the antibiotic choice to ensure that the spectrum of activity is adequate. If the spectrum is inadequate, this will be communicated to the treating physicians. To avoid differentially influencing antibiotic choices and clinical decision-making, the randomization assignment will not be communicated to the study research coordinator, study critical care or infectious diseases investigators or clinicians until the end of day 7. The ICU research coordinator at each site will visit daily to ensure protocol adherence (antibiotics are stopped at the pre-specified date (end of the 7th or 14th day) and not earlier (Figure 1).

**Figure 2 Fig1:**
[figure not shown]
Determination of day 7 of antibiotic treatment. Multiple scenarios are provided to determine how day 7 of antibiotic treatment will be determined based on days of receipt of adequate antibiotic treatment after collection of the positive blood culture. Adequacy of treatment will only be measurable after the culture and susceptibility result has been finalized.

Calculating day 7 of adequate antibiotics is a complex procedure; there are multiple potential scenarios of adequate and inadequate antibiotic treatment days prior to the culture results being finalized. Figure 2 demonstrates some of the possible scenarios, to illustrate calculation of day 7 from the positive blood culture collection date. The day 7 unblinding date will be calculated as the cumulative number of calendar days the patient receives adequate antibiotics after the positive blood culture collection date. Adequacy of antibiotics will only be definable after the final susceptibility report is available. If a patient received inadequate antibiotics after the positive blood culture collection and before the culture is finalized (Figure 2, scenario 3), day 7 date will be calculated from the date adequate antibiotics were started, which should be immediately after the culture is finalized. If a patient received adequate antibiotics for one day after positive blood culture collection and then was switched to inadequate antibiotics until the culture was finalized (Figure 2, scenario 7), then this one day of adequate antibiotic after positive culture collection will still be counted in the calculation of the day 7 date. Once the culture is finalized, adequate antibiotic treatment should be started/continued without any break until the completion of the assigned treatment duration based on study arm. Discontinuation or missed treatment before the completion of the assigned treatment duration will be considered to be a protocol violation.

